### 2.5. Secondary Outcomes

#### 2.5.1. Lifestyle Behaviors

Lifestyle behaviors will be assessed by self-administered questionnaires. Details of lifestyle behavior assessments have already been discussed in the intervention section.

#### 2.5.2. Changes in Biomedical Characteristics

 Biomedical data collected from hospital records at baseline and at 12 months (age, BMI, waist circumference, and levels of HbA_1C_, fasting blood glucose, triglyceride, LDL cholesterol, and HDL cholesterol) will be used in the analyses.

#### 2.5.3. Change in Risk Perception and Recognition About Diabetes, and Attitude towards Its Prevention

Subjects' perception and recognition about diabetes and attitude towards its prevention will be assessed before GC session (baseline for these variables) and 1 week after the session in order to evaluate the effect of GC on subjective aspect.

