#### 2.3.2. Printed, Computer-Tailored Lifestyle Intervention

Lifestyle intervention in this study features tailored and concrete lifestyle recommendations in a computer-based, non-face-to-face format. The intervention will use Lifestyle Intervention Support Software for Diabetes Prevention (LISS-DP). Contents of LISS-DP are developed based on lifestyle intervention protocol for secondary or tertiary prevention in type 2 diabetes patients, which has been developed by one of authors [52, 53].

The intervention strategy consists of the following processes: (1) lifestyle and background data collection by self-administered questionnaire; (2) generation of tailored recommendations; (3) output of tailored recommendations; (4) delivery of the recommendations via mail.

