#### 2.3.3. Control Group

Subjects allocated to the control group will receive conventional routine care during the study period, including disclosure of medical checkup results and general information about diabetes prevention. This conventional routine care will also be provided to the other two groups. The genetic counseling booklet and three lifestyle advice sheets will be sent to subjects in the control group after the end of the study period.

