### 2.6. Data Collection

Data collected at the time of recruitment and at 1 week and 3, 6, and 12 months after recruitment will be used in this study. Background characteristics will be assessed at the time of recruitment: whether he/she has impaired glucose tolerance, abnormalities of lipid metabolism, hypertension or hyperuricemia; living status; occupational status; educational status. Baseline values for outcome measures related to lifestyle behaviors will be collected at 1 week after recruitment because participants must spent more than 15 minutes to answer the questionnaire for lifestyle assessment, and it is infeasible to order them about completing it during medical checkup. All questionnaires will be sent and returned via mail, except for the questionnaire completed at the time of recruitment. We will phone participants or mail a reminder if the questionnaire has not been returned until deadline, four weeks after each questionnaire had been sent. Biomedical data were collected at recruitment and will be collected again at 12 months.

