### 2.11. Statistical Analysis

Statistical analysis will be carried out on an intention-to-treat basis. We will summarize continuous variables using means and standard deviations, and categorical variables using counts and percentages.

The effects of GC will be investigated by comparing the GC&LI and LI groups. Similarly, the effects of LI will be investigated by comparing the LI and control groups. Primary outcomes will be analyzed by ANCOVA, adjusting for baseline values. Differences between groups in secondary outcomes at each assessment point will be analyzed by the Student's *t*-test for continuous variables or the Mann-Whitney *U* test for ordinal variables.

In all tests, a *P* value of <0.05 by two-tailed test will be considered significant. Analysis will be performed using SAS 9.2 (SAS Institute, Cary, NC, USA) software for windows.

All study protocols have been approved by the institutional review board of the School of Medicine, The University of Tokyo and Social Insurance Chuo General Hospital. Clinical Trial Registration: UMIN-CTR: UMIN00003589, UMIN00003636.

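### The 1-week perception and attitude outcomes are tested without adjustment for the pre-counseling score collected as their baseline, which wastes precision in the GC&LI vs LI comparison

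*Protocol article*

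**What the plan says.** Section 2.5.3 lists perception and recognition of diabetes, and attitude towards its prevention, as secondary outcomes. They "will be assessed before GC session (baseline for these variables) and 1 week after the session", with the stated aim of judging what counseling does on the subjective side. The section heading calls the outcome a change.

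Section 2.11 sets the contrast: "The effects of GC will be investigated by comparing the GC&LI and LI groups". It gives baseline-adjusted ANCOVA to the primary outcomes. For the rest it says: "Differences between groups in secondary outcomes at each assessment point will be analyzed by the Student's" *t*-test if continuous, or by the Mann-Whitney test if ordinal. It mentions no covariate for secondary outcomes and makes no exception for those measured at 1 week.

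On timing, section 2.6 states: "Baseline values for outcome measures related to lifestyle behaviors will be collected at 1 week after recruitment".

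**The concern.** A score is collected before counseling and named as the baseline for these variables, yet the stated test has no place for it. A test of scores at an assessment point compares 1-week values only, so stable differences between people in how they perceive risk stay in the error term. The same section removes that variation for the primary outcomes.

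This is the only outcome that the article ties directly to the subjective effect of counseling. The background section treats recognition of risk as the step that leads to preventive behavior. If counseling shows no effect on compliance, the 1-week result helps to tell whether counseling failed to change awareness or awareness failed to change behavior. An imprecise result weakens that reading.

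A second question is whether the control arm could add information at 1 week, since LI does not seem to have started by then.

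**Working it through.** **The plan's own figure.** Section 2.7 gives 64 per arm for 0.5 SD, 80% power and 5% significance (two-sided, section 2.11). The normal approximation gives n = 63 and the t-test solution is 63.77, hence 64. With 10% dropout, 64/0.9 = 71.1, hence 72. Both figures reproduce.

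**Gain from the baseline score.** Let ρ be the correlation between the pre-counseling and 1-week scores, with equal SDs at both times. The article gives no ρ, so a range is assumed. Relative to the variance of the 1-week score:

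- unadjusted 1-week score: 1
- change score: 2(1 − ρ)
- ANCOVA: 1 − ρ²

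| Assumed ρ | Change score variance | ANCOVA variance | ANCOVA information vs unadjusted, 1/(1 − ρ²) | ANCOVA information vs change score, 2/(1 + ρ) |
|---|---|---|---|---|
| 0.3 | 1.40 | 0.91 | 1.10 (+10%) | 1.54 (+54%) |
| 0.5 | 1.00 | 0.75 | 1.33 (+33%) | 1.33 (+33%) |
| 0.7 | 0.60 | 0.51 | 1.96 (+96%) | 1.18 (+18%) |

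ANCOVA is the most precise of the three at each ρ. A change score is noisier than the raw 1-week score when ρ is below 0.5. These are large-sample figures for a continuous score with a linear relation.

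**Has LI started at 1 week?** The first two steps of LI are listed as "1) lifestyle and background data collection by self-administered questionnaire; (2) generation of tailored recommendations" (section 2.3.2), so a sheet cannot be produced before the questionnaire is back. Section 2.6 first collects the lifestyle measures at 1 week and treats them as baseline. On control, section 2.3.3 says of routine care: "This conventional routine care will also be provided to the other two groups"; the booklet and advice sheets "will be sent to subjects in the control group after the end of the study period". At the 1-week assessment LI and control therefore appear to have had the same care. This is inferred from the order of steps, because no mailing date is given for the first sheet. It also assumes that the perception items are answered no later than the lifestyle questionnaire.

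**Gain from adding control.** Section 3 reports lifestyle questionnaire returns of 69 (GC&LI), 63 (LI) and 57 (control). Returns of the perception items are not reported, so these counts are an assumption.

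- GC&LI vs LI: 1/(1/69 + 1/63) = 32.9
- GC&LI vs LI and control: 1/(1/69 + 1/120) = 43.8
- Ratio: 43.8/32.9 = 1.33

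Noncentral-t power, before any baseline adjustment, rises from 81% to 91% at 0.5 SD and from 62% to 75% at 0.4 SD.

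**Risk in adding control.** Suppose that LI participants, who await advice, answer differently from controls by e SD (an assumption). Control supplies 57/120 = 47.5% of the combined comparator, so the estimate shifts by 0.475e. The gain in mean squared error is gone when (0.475e)² = 1/32.9 − 1/43.8 = 0.0076, that is e = 0.087/0.475 ≈ 0.18. An LI vs control check has information 1/(1/63 + 1/57) = 29.9. At 0.18 SD the standardized difference is 0.18 × √29.9 = 0.98, which gives power of about 17%.

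**The case against.** The case for leaving the plan alone has four parts.

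- **Validity and power.** GC&LI vs LI is a concurrent randomized comparison, and at 69 vs 63 it already has 81% power at 0.5 SD, the trial's own planning standard. This stands: the loss is one of efficiency.
- **The baseline may be used.** The heading says *Change*, and a t-test or Mann-Whitney test can be run on change scores. This stands in part. A reader might infer that the plan throws the baseline score away, but the text is ambiguous and does not support that. Under the change-score reading, ANCOVA is still more precise.
- **A condensed article.** Covariates for secondary outcomes are often left to a fuller document. Here, however, the article itself names the tests and assigns baseline adjustment to the primary outcomes only, so the choice is stated.
- **Control should not be pooled by default.** A reader might infer from the 33% gain that LI alone is the wrong comparator and that the combined group should be the main analysis. The documents do not support that. Participants know their allocation (section 2.9) and the outcomes are self-reported. Lifestyle questionnaire returns were 92% and 90% in the two LI-offered arms but 80% in control (LI vs control, Fisher p = 0.15). An expectation difference of about 0.18 SD would cancel the gain, and the available check could hardly detect it. GC&LI vs LI holds the expectation of advice constant and matches the contrast used elsewhere for GC. Section 2.5.3 also does not say outright that control completes these items at 1 week. This objection stands, so pooling can only be supplementary.

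**Conclusion.** The point holds as a modest loss of precision. Section 2.11 tests the 1-week perception, recognition and attitude outcomes without adjusting for the baseline that section 2.5.3 collects. Adjustment would give about 10%, 33% or 96% more information than an unadjusted 1-week test at assumed correlations of 0.3, 0.5 or 0.7. Against change scores the gain is about 54%, 33% or 18%. The result assumes that the pre-counseling score is available in both GC&LI and LI.

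At a correlation of 0.5, adjustment gains as much as adding the control arm would (1.33 in both cases) and leaves the randomized GC&LI vs LI comparison intact. The choice of LI as comparator is neither an error nor a source of bias. The figure for adding control rests on assumed returns of 69/63/57 and on the inference that no advice sheet exists at 1 week.

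**What to change.** Add to section 2.11 that the 1-week perception, recognition and attitude outcomes are compared between GC&LI and LI with adjustment for the pre-counseling score, by ANCOVA if continuous or proportional odds regression if ordinal. State that this replaces the unadjusted test for these outcomes.

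Optionally, name a supplementary analysis of GC&LI vs LI and control combined, with the same adjustment. Show LI vs control at 1 week beside it, report returns by arm, and state that participants are unblinded and that the LI vs control check has little power to show that pooling is safe.

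The cost is a sentence or two of wording, with no new data and no more participants. It should be fixed before 1-week results are examined by arm.

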### 2.6. Data Collection

Data collected at the time of recruitment and at 1 week and 3, 6, and 12 months after recruitment will be used in this study. Background characteristics will be assessed at the time of recruitment: whether he/she has impaired glucose tolerance, abnormalities of lipid metabolism, hypertension or hyperuricemia; living status; occupational status; educational status. Baseline values for outcome measures related to lifestyle behaviors will be collected at 1 week after recruitment because participants must spent more than 15 minutes to answer the questionnaire for lifestyle assessment, and it is infeasible to order them about completing it during medical checkup. All questionnaires will be sent and returned via mail, except for the questionnaire completed at the time of recruitment. We will phone participants or mail a reminder if the questionnaire has not been returned until deadline, four weeks after each questionnaire had been sent. Biomedical data were collected at recruitment and will be collected again at 12 months.

### 2.7. Sample Size

We had conducted preliminary intervention study for offspring of type 2 diabetes patient [24]. The intervention in preliminary study was conducted in mail-delivered style, similar to current study, while advice sheet was made by a dietician and a medical fitness therapist in handwriting. After three-times intervention during 6 months, −1.0 SD change was observed in primary outcome (total energy intake). Intervention in current study is computer-based, it means less tailored to individual participant than preliminary study. So observed effect in this study is expected to be modest compared to preliminary study. We calculated the necessary sample size to be 64 per study arm to detect a moderate effect size (0.5 SD), with 80% power at the 5% significance level. Assuming a dropout rate of 10% from the results of a previous similar study [37, 46], 72 participants are needed for each arm.

### 2.8. Randomization

Subjects were randomly allocated to one of three equal-sized groups. Random allocation was performed using a table of random numbers. Researchers were blinded to characteristics of the subjects during randomization.

### 2.9. Blinding

Group allocation obviously cannot be blinded to participants in this study. Therefore, this study will be conducted with a single-blinded design; group allocation was blinded to the clinical diabetes educator and researcher who will analysis the data.

### 2.10. Data Management

 Once questionnaire will be sent back to research institute, one of researchers immediately check the validity of responses. If missing value or outlying response was found, researcher would phone participant to correct these incomplete response. To avoid human error in data input, two research assistants independently input all the responses into computer. After checking one dataset against another one and confirming perfect matching, the dataset will be input into LISS algorithm.

### 2.11. Statistical Analysis

Statistical analysis will be carried out on an intention-to-treat basis. We will summarize continuous variables using means and standard deviations, and categorical variables using counts and percentages.

The effects of GC will be investigated by comparing the GC&LI and LI groups. Similarly, the effects of LI will be investigated by comparing the LI and control groups. Primary outcomes will be analyzed by ANCOVA, adjusting for baseline values. Differences between groups in secondary outcomes at each assessment point will be analyzed by the Student's *t*-test for continuous variables or the Mann-Whitney *U* test for ordinal variables.

In all tests, a *P* value of <0.05 by two-tailed test will be considered significant. Analysis will be performed using SAS 9.2 (SAS Institute, Cary, NC, USA) software for windows.

All study protocols have been approved by the institutional review board of the School of Medicine, The University of Tokyo and Social Insurance Chuo General Hospital. Clinical Trial Registration: UMIN-CTR: UMIN00003589, UMIN00003636.

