(1) Lifestyle and Background Data Collection by Self-Administered QuestionnaireLISS-DP requires information about the subject's current diet and PA to identify risky or favorable behavior. Current lifestyle behaviors will be assessed using a self-administered questionnaire. The questionnaire is based on two measurement scales: evaluation scale for self-management behavior related to physical activity of type 2 diabetic patients (ES-SMBPA-2D) [54] and Dietary Self-Management Behavior Questionnaire (DSBQ) [55]; which were developed by the authors. These scales measure dietary and PA self-management behaviors in diabetic patients and consist of 32 and 91 items, respectively. We modified these scales to assess preventive dietary and PA behaviors in healthy relatives of patients with type 2 diabetes. Items were chosen for each scale according to the following criteria: dietary behavior shown in previous research to have a significant relationship with total energy intake [52, 53], PA behavior shown to have a significant relationship with energy expenditure [54], and important preventive behaviors as judged by an expert panel. As a result, a lifestyle assessment questionnaire consisting of 53 items was developed, with 15 items assessing “recommended dietary behaviors (RD)” (Table 1), 21 items assessing “recommended physical activity behaviors (RP)” (Table 2), 16 items assessing “nonrecommended dietary behaviors (ND)” (Table 3), and a single item assessing “nonrecommended physical activity behavior (NP)” (Table 3). Questionnaires ask the subjects to indicate the frequency of each behavior on five-point scale which will be converted to a numerical score: never (0), rarely (1), sometimes (2), often (3), or always (4).

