### 2.4. Primary Outcomes

#### 2.4.1. Changes in Total Energy Intake, Fat-Energy Ratio, and Physical Activity

The primary outcomes of this study are changes in total energy intake, fat-energy ratio, and physical activity levels between baseline and the end of the intervention period. These variables will be measured by self-administered questionnaires. The questionnaires include a dietary measurement scale (Modified-Ministry of Health and Welfare-Food Questionnaire (M-MHW-FQ)) and a physical activity scale (International Physical Activity Questionnaire (IPAQ)). The M-MHW-FQ has been shown to be a reliable method of calculating energy intake and fat-energy ratio [56]. The IPAQ has been shown to be a valid method of assessing physical activity across various life activities, including during leisure activities [57–59].

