## 3. Results

Figure 1 shows a flow diagram of subject enrollment and initial data collection. During the recruitment period, 538 eligible examinees visited the outpatient department. Of these, 322 (59.8%) declined to participate in the study, leaving 216 subjects who were randomly allocated to one of three groups and completed initial data collection: GC&LI (*n* = 75), LI (*n* = 70), and control (*n* = 71). The baseline questionnaire about lifestyle behaviors was completed by 69 subjects (92%) in the GC&LI group, 63 subjects (90%) in the LI group, and 57 subjects (80%) in the control group.

Table 4 shows the baseline characteristics of subjects. Overall, 61.1% of subjects are male, and the mean age is 45.8 ± 7.8 years. The mean BMI indicates that subjects are in the nonobese range (22.5 ± 3.0 kg/m^2^). All the biomedical characteristics were in the normal range. Mean energy intake was 1777.4 ± 420.8 kcal/day, and fat/energy ratio was 28.9 ± 6.6%. Mean energy expenditure by physical activity was 279.0 ± 510.2 kcal/day.

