*n* = 69 in GC&LI, *n* = 63 in LI, *n* = 57 in control.

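### The analysis is called intention-to-treat, but baseline-adjusted ANCOVA on change scores cannot, as stated, include the 27 of 216 randomised subjects without a baseline value

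*Protocol article*

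**What the plan says.** Section 2.11 of the protocol article sets both the principle and the model. The principle is "Statistical analysis will be carried out on an intention-to-treat basis". The model is "Primary outcomes will be analyzed by ANCOVA, adjusting for baseline values". Section 2.4.1 defines the primary outcomes as "changes in total energy intake, fat-energy ratio, and physical activity levels between baseline and the end of the intervention period".

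Section 2.6 has the lifestyle baseline collected one week after recruitment, by mail, with a phone or mail reminder to late returners. Section 2.9 accepts that participants cannot be blinded to their group.

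Section 3 gives 75, 70 and 71 subjects randomised to GC&LI, LI and control. The baseline lifestyle questionnaire was completed by "69 subjects (92%) in the GC&LI group, 63 subjects (90%) in the LI group, and 57 subjects (80%) in the control group". The footnote to Table 4 gives the same three counts for baseline energy intake, fat-energy ratio and physical activity.

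Section 2.3.2 says that the software which generates the tailored advice needs information on the subject's "current diet and PA to identify risky or favorable behavior". The article gives no rule for analysing a randomised subject who has no baseline value.

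**The concern.** A subject without a baseline has no change score and no covariate value. The model in section 2.11 therefore has no place for that subject, whatever follow-up he or she provides. The intention-to-treat label and the stated model do not agree.

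Returning the baseline form is an act after randomisation by someone who is not blinded, and the return rate differs between arms. In the two arms with lifestyle intervention, questionnaire data are also the input for the first tailored advice sheet. A comparison restricted to returners is therefore partly conditioned on engagement with the programme. At stake are the protection that randomisation gives to the LI versus control contrast, and some precision.

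**Working it through.** **Reproducing the plan's own figure.** Inputs from section 2.7: 0.5 SD, 80% power, two-sided 5%. The t-based solution is 63.77, so 64 per arm. With 10% dropout, 64/0.9 = 71.1, so 72 per arm. Both stated figures reproduce.

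**Who has a baseline (section 3, Table 4 footnote).**
- GC&LI: 75 − 69 = 6 missing, 6/75 = 8.0%
- LI: 70 − 63 = 7 missing, 7/70 = 10.0%
- Control: 71 − 57 = 14 missing, 14/71 = 19.7%
- Total: 27 missing, 27/216 = 12.5%; 189 have a baseline

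The overall means in section 3 confirm the 189. Weighting the arm means by 69/63/57 gives (69×1782.8 + 63×1689.9 + 57×1867.7)/189 = 1777.4 kcal/day for energy intake and 279.0 kcal/day for physical activity, both as stated. Weights of 75/70/71 would give 1780.6 and 283.0. The fat-energy ratio is 28.9% either way.

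**Imbalance in the planned contrasts (Fisher exact).** LI versus control, 7/70 against 14/71: p = 0.15. GC&LI versus LI, 6/75 against 7/70: p = 0.77. The three-arm chi-square gives p = 0.075.

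**Possible shift in the estimate.** Suppose that non-returners differ from returners by k SD in outcome after baseline adjustment, equally in each arm. Restricting to returners then shifts a contrast by k times the difference in missing proportions.
- LI versus control: k × (0.197 − 0.100) = 0.097k, so 0.05 SD at k = 0.5 and 0.10 SD at k = 1.0
- GC&LI versus LI: k × (0.100 − 0.080) = 0.020k, so 0.01 to 0.02 SD

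The values of k are assumptions; nothing in the article informs them.

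**Unadjusted power at 0.5 SD (two-sample t, before follow-up loss).** The noncentrality is 0.5/√(1/n₁ + 1/n₂).
- LI versus control, 63/57: 0.5/0.183 = 2.74, power 77.4%; at 70/71 it is 83.8%
- GC&LI versus LI, 69/63: power 81.3%; at 75/70 it is 84.8%

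If a further 10% were lost at follow-up (assumption), these would fall to about 73% and 77%. Covariate adjustment works the other way. At an assumed baseline-outcome correlation of 0.3 to 0.5, the effective effect size is 0.5/√(1 − 0.09) = 0.52 to 0.5/√(1 − 0.25) = 0.58, and power at 63/57 is about 81% to 88%.

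**The case against.** The best defence is that the article is condensed. It nowhere says that subjects without a baseline are excluded. Dropping them is what the model does by default, and a method for missing baselines could sit in an analysis plan that is not shown. It is also true that complete-case ANCOVA is not biased when missingness depends only on arm and baseline value. Bias needs dependence on the outcome beyond these. Subjects who ignored the first questionnaire may also return none later, and then no model recovers them.

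These points limit the concern but do not remove it. The article itself fixes the label, the model and the change-score definition, and it reports the loss as already observed.

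A reader might infer more than the article supports:
- **That the 13 non-returners in GC&LI and LI never started their intervention.** Without questionnaire data the first tailored sheet could not be generated, but further questionnaires and sheets follow, so a later start is not ruled out. Counselling in GC&LI came after consent and did not depend on the form. The software uses a 53-item behaviour questionnaire, whereas the primary outcomes use separate diet and activity instruments. The matching counts suggest one mailing, but the article does not say so.
- **That differential loss is proven.** Pooling both LI arms against control (13/145 versus 14/71) gives p = 0.03, but section 2.11 plans no such contrast.
- **That the baseline energy gap between LI and control shows selection.** The gap is 1867.7 − 1689.9 = 177.8 kcal/day, or 0.42 SD on the overall SD of 420.8. For unequal return alone to produce it, non-returners would have to differ by 0.42/0.097, about 4.3 SD. Chance is the more plausible source, and ANCOVA adjusts for such a gap.
- **That the trial is clearly underpowered.** The fair benchmark is the planned 80%, not the 84% that assumes no loss, and adjustment may recover the shortfall.

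**Conclusion.** The concern holds in limited form. As written, the primary model can use at most 189 of 216 randomised subjects (87.5%), so it is a complete-case analysis carrying an intention-to-treat label. This rests on the article's own counts and definitions, and on no missing-baseline method being applied.

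LI versus control is the contrast mainly affected. For GC&LI versus LI the missing proportions are close and any shift from this source is small.

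The direction and size of bias are unknown. The shift of 0.05 to 0.10 SD in LI versus control assumes a residual difference of 0.5 to 1.0 SD, equal across arms; that is 10% to 20% of the 0.5 SD design effect. The power shortfall is about 3 points against plan (77% versus 80%), before follow-up loss and without credit for adjustment.

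**What to change.** Include every randomised subject who has any value of the outcome, by one of two routes:
- A longitudinal model with the baseline as one of the responses. For LI versus control, use a common baseline mean. For GC&LI versus LI, do not impose that constraint, because the baseline is taken after counselling and may already reflect it.
- Multiple imputation of the missing baseline from recruitment variables such as sex, age and BMI, which Table 4 reports on all 216, followed by the planned ANCOVA. Use the follow-up value as the response; with baseline as a covariate, the group effect is the same as for change.

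Keep complete-case ANCOVA as a sensitivity analysis, and add an analysis that shifts the missing values by arm. Confirm that follow-up questionnaires go to subjects who did not return the baseline form; section 2.6 states no restriction, but the analysis depends on it. If neither route is taken, call the primary analysis complete-case (modified) and drop the intention-to-treat wording.

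The cost is a change of text and some programming, with no new participants. The price is reliance on a missing-at-random assumption, which the shift analysis is there to test. The common baseline mean also assumes that knowing the allocation did not alter reported behaviour in the first week.
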